## Anthropometric measures and blood pressure

We will measure weight on a calibrated digital scale, waist and hip circumference at the baseline and follow-up clinic visits. We will measure height by stadiometer at the baseline clinic visit. Blood pressure is measured while sitting quietly and after resting quietly for a few minutes, and with both feet on the ground, using an Omron digital automatic standard blood pressure monitor. A large cuff is used if required. Blood pressure on both arms will be obtained initially and the higher blood pressure of the two will be used. Three measurements will be taken, and the average of the last two measurements is recorded. If there is >10mm/Hg or >6mm/Hg difference in systolic or diastolic blood pressure respectively, the participant is asked to rest quietly for five minutes and blood pressure measurement is repeated ([48](#_ENREF_48)).

Anthropometric measures and blood pressure will be measured according to standard procedures as outlined in http://www.cdc.gov/NCHS/data/nhanes/nhanes_07_08/manual_an.pdf

Data will be entered by the Research assistant into the Redcap database.

## Measures of insulin resistance

Participants will attend for a 2 hr Oral Glucose Tolerance Test and Insulin test prior to attending for the baseline visit and at the 3-month follow-up. Insulin will be calculated using the Area Under the Curve (AUC) method. Participants will attend for these tests at accredited pathology collection centres (Laverty Pathology).

Biomarkers that are related to insulin resistance and PCOS are collected at the same time and include Sex Hormone Binding Globulin, total and free testosterone.

Abnormal results will be followed up by phone and letter to the participant and GP by [name], who is a practising GP. Participants will be asked to attend their GP for follow-up. If participants are diagnosed with diabetes, they are excluded from the trial.

## Heart Rate Variability

Heart Rate Variability will be calculated from electrocardiogram (ECG) recordings during the clinic visits.

ECG recordings take place in the Headbox labs on the Campbelltown campus, Western Sydney University. Women will be asked to avoid caffeine and smoking for at least two hours prior to HRV measurement. The total time for ECG recordings is up to 30 minutes.

A research assistant, supervised by CI [name], an experienced psychophysiologist with substantial expertise in measures of ANS physiology, will conduct ECG recordings. ECG electrodes will be placed on the sternum and lower left ribs. Five minutes of seated resting-state 2-lead ECG will be recorded via bipolar Ag/AgCl electrodes with a Compumedics Neuroscan Synamps 2 Digital Signal Processing System. Interbeat intervals (IBIs) are calculated from the ECG trace before a fast-fourier transformation is then applied to convert HRV data from time to frequency domain. HRV frequency bands will be defined as Very Low Frequency (< 0.04 Hz), Low Frequency (LF; 0.04 – 0.15 Hz), and High Frequency (HF; 0.18 – 0.40 Hz). LF/HF ratio will also be calculated as a measure of sympathovagal balance.

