**Heart Rate Variability: a surrogate marker of autonomic tone**

Sympathetic tone can be measured directly using microneurography; however, this procedure limited by its invasive nature. Heart rate variability (HRV) provides non-invasive measures of both parasympathetic (high frequency/HF component) and sympathetic tone (low frequency/LF component) [16, 18]. Several sham-controlled RCTs on acupuncture for a variety of clinical conditions suggest that it is more efficacious than sham in reducing sympathetic tone as measured by HRV[18-20]. To date, the effect of acupuncture on HRV in women with PCOS has not been evaluated, although electro-acupuncture improved HRV and restored oestrous cycling compared to sham handling in a recent rat study[21].

Our partner's previous research showed that AEA resulted in improvement in HRV LF/HF ratios over the course of the protocol intervention, implying improved sympathovagal balance[1], however this was measured using ambulatory HRV monitoring, which has not been validated against the gold-standard of electrocardiogram (ECG) recordings.

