### Secondary Objectives

2) Determine an effect size for acupuncture and lifestyle vs lifestyle alone and examine for a trend between groups for change in body weight and BMI.

3) Explore the impact of body electro-acupuncture and auricular electro-acupuncture on sympathetic tone and insulin resistance

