### Secondary Endpoints

Difference between groups for anthropometric measures, health-related quality of life, menstrual cycles, psychological measures, self-efficacy and locus of control; measures of insulin resistance; and heart rate variability; free and total testosterone and free androgen index.

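### The HRV bands leave 0.15–0.18 Hz unassigned without explanation, which can only lower HF and raise LF/HF relative to contiguous bands

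*Protocol*

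**What the plan says.** Protocol section 8.3 (Heart Rate Variability) gives the recording, the transform and the bands:

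- Recording: "Five minutes of seated resting-state 2-lead ECG will be recorded".
- Transform of the interbeat intervals: "a fast-fourier transformation is then applied to convert HRV data from time to frequency domain".
- Lowest band: "HRV frequency bands will be defined as Very Low Frequency (< 0.04 Hz".
- The other two bands: "Low Frequency (LF; 0.04 – 0.15 Hz), and High Frequency (HF; 0.18 – 0.40 Hz".
- Derived measure: "LF/HF ratio will also be calculated as a measure of sympathovagal balance".

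No other section gives band limits. The Background (section 1.1) says only what the bands stand for, describing HRV as giving "non-invasive measures of both parasympathetic (high frequency/HF component) and sympathetic tone (low frequency/LF component".

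HRV is listed among the secondary endpoints in section 2.2.2: "measures of insulin resistance; and heart rate variability; free and total testosterone and free androgen index". It serves the third objective in section 2.1.2: "Explore the impact of body electro-acupuncture and auricular electro-acupuncture on sympathetic tone and insulin resistance". The primary endpoint in section 2.2.1 concerns feasibility, credibility, acceptability and safety.

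**The concern.** The three bands look like a partition of the spectrum up to 0.40 Hz, but they are not one. VLF ends where LF begins, at 0.04 Hz. LF ends at 0.15 Hz and HF begins at 0.18 Hz. The protocol itself sets these limits, so an analyst who follows it will leave out the power in between.

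The omitted strip matters because of what HF is taken to mean. The protocol reads HF as the parasympathetic component and LF/HF as autonomic balance. If HF power is concentrated around the breathing frequency, a woman breathing at 9.0–10.8 breaths/min has the centre of that power in the strip. Her HF would be understated and her LF/HF overstated. The recordings are seated and at rest, and breathing rate appears neither in section 8.3 nor in the schedule in Appendix 1, so there is no planned way to see or adjust for this.

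The study aims to analyse about 10 women per arm and to inform a larger trial. One or two slow breathers could move an arm's mean, and an unexplained band definition could be carried forward.

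**Working it through.** **Inputs from protocol section 8.3.** VLF < 0.04 Hz; LF 0.04–0.15 Hz; HF 0.18–0.40 Hz; five-minute recording (300 s); FFT. The protocol states no breathing rate and no spectral shape, so those used below are assumptions.

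**The gap.**
- Width: 0.18 − 0.15 = 0.03 Hz.
- As a rate: 0.15 × 60 = 9.0 and 0.18 × 60 = 10.8 cycles/min.
- If the whole recording is transformed as one segment, the resolution is 1/300 = 0.0033 Hz. The gap is then 0.03 × 300 = 9 resolution steps wide, and eight frequency points (46/300 to 53/300) lie strictly inside it. The gap is therefore resolvable and not a rounding matter.

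**Direction.** Let G ≥ 0 be the power in the gap, H the HF power as written and L the LF power. If HF started at 0.15 Hz it would be H + G. L is the same under both definitions. Hence H ≤ H + G and L/H ≥ L/(H + G). With s = G/(H + G), the share of contiguous HF that is omitted, LF/HF as written equals the contiguous value multiplied by 1/(1 − s).

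**Size, flat spectrum (assumption).** HF width as written is 0.40 − 0.18 = 0.22 Hz; contiguous, it is 0.40 − 0.15 = 0.25 Hz. Then s = 0.03/0.25 = 12%, and LF/HF is multiplied by 0.25/0.22 = 1.14.

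**Size, single Gaussian respiratory peak (assumption).** With the peak centred at f = rate/60 Hz with standard deviation σ,

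s = [Φ((0.18 − f)/σ) − Φ((0.15 − f)/σ)] / [Φ((0.40 − f)/σ) − Φ((0.15 − f)/σ)].

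| Breaths/min | s, σ = 0.015 Hz | s, σ = 0.02 Hz | s, σ = 0.03 Hz | LF/HF multiplied by |
|---|---|---|---|---|
| 10 | 78.4% | 68.3% | 53.8% | 2.16–4.63 |
| 10.8 | 48.8% | 46.4% | 40.6% | 1.68–1.95 |
| 12 | 9.1% | 15.3% | 21.5% | 1.10–1.27 |
| 14 | 0.0% | 0.4% | 3.5% | 1.00–1.04 |
| 16 | 0.0% | 0.0% | 0.2% | 1.00 |

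The omission is small at 14 breaths/min or faster, moderate at 12 and large near 10.

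**Effect on a contrast.** If s is the same in every arm and at both visits, every HF value is multiplied by (1 − s) and every LF/HF value by 1/(1 − s). Ratios between arms or visits are unchanged, and raw differences are rescaled by that one factor without changing sign. Distortion therefore needs s to differ between arms or visits, that is, a different prevalence of slow breathing.

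**The case against.** A reader might infer that 0.18 Hz is an error and that HF and LF/HF are therefore calculated wrongly. The document does not show that. No other section gives band limits, so nothing contradicts 0.18 Hz, and calling it wrong would need an outside standard. The fact that VLF and LF meet hints at a slip but does not prove one. The bands are stated in advance, and nothing applies them differently by arm or visit, so both measures can be computed and compared as defined. This stands.

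A reader might also infer that improved parasympathetic tone would be reported as worsened balance. That would require treatment to slow breathing into the strip, and to do so differently between arms. The protocol says nothing about either treatment changing breathing rate, and the second recording is made after treatment is complete (section 7.1.1, post-intervention visit), not during needling. It remains a possibility only.

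Contiguous bands also do not remove all dependence on breathing. A woman breathing below 9/min would have her respiratory peak in LF under either definition. That stands too, and it limits what the fix achieves.

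None of this explains the gap. Applying the same bands to everyone does not guarantee an undistorted contrast when the omitted share depends on a quantity that is not listed as measured. Nor is this detail left to an analysis plan, since the protocol fixes the limits itself.

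**Conclusion.** The gap is certain: as written, 0.15–0.18 Hz belongs to no band and no reason is given. The direction is also certain relative to contiguous bands. The size is not known, because it rests on assumed spectral shapes and breathing rates. The assumptions span from almost nothing at 14 or more breaths/min to more than half of HF at 10/min, and the flat-spectrum figure of 12% should not be read as typical.

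Whether any comparison in the trial is affected depends on slow breathing differing between arms or visits, for which the protocol gives no evidence either way. The point is minor: HRV is one of many secondary endpoints, under an exploratory objective, in a trial whose primary endpoint is feasibility. It is still worth settling, because it concerns a stated rule and is almost free to change.

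**What to change.** Before HF and LF/HF are analysed, amend section 8.3 so that HF starts where LF ends (0.15–0.40 Hz). If 0.18 Hz was intended, say why the strip is left out, and report HF and LF/HF computed with 0.15–0.40 Hz as a sensitivity analysis.

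The cost is one number in the protocol and a re-run of the spectral script on the recorded ECG data. No new measurement, visit or participant is needed.

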## Clinical Hyperandrogenism

The Ferriman-Gallwey scoring system was developed by Ferriman and Gallwey in 1961 and is widely used to evaluate and quantify hirsutism in women. The method was modified and now incorporates nine body regions (excludes legs and forearms) for the assessment of hair growth, rated from 0 (no growth of terminal hair) to 4 (extensive hair growth) in each of the nine locations. The FG score will be assessed by the research assistant and/or by the woman herself (by indicating on a diagram which of the diagrams best represents her current level of hair growth). {Ferriman, 1961 #4348}

## Other outcomes collected during clinic visits

The following data will be collected during clinic visits. Participants may use an online survey or paper surveys. Data on paper surveys will then be manually entered into Redcap by the Research assistant.

- Health related quality of life – the Modified PCOS Questionnaire
- Global quality of life - EQ-5D
- Psychological Symptoms – the DASS 21
- Weight self efficacy – the Weight Efficacy Lifestyle Questionnaire short form
- Internal locus of control – the Internal Health Locus of Control questionnaire
- Demographic questionnaire – see Appendix

## Credibility, expectancy and perceived treatment allocation

Immediately following the first treatment, participants will complete the Credibility and Expectancy Questionnaire and question on perceived treatment allocation. This can be done online at the acupuncturist’s clinic or via email, or on paper and returned to the research assistant by fax or email.

## Other outcomes

Accelerometers will be collected from participants at the follow-up treatment visit and data will be downloaded electronically.

Data on compliance with the lifestyle coaching program will be provided by Gethealthy NSW at baseline and 3 months.

## Participant Reimbursement

Participants will be reimbursed $40 in total for travel costs associated with the study. At the second and final clinic visit, participants will be offered the opportunity to claim a maximum of $40 by completing a standard invoice template which will be submitted to NICM HRI administration to be processed. The payment is made by direct bank deposit to the participants' nominated bank account.

# Statistics and Data Analysis

## Sample Size Calculation

***Sample size*** has been determined to answer the research questions regarding an estimate of the effect size, and recruitment, retention and adherence rates. 39 participants will be recruited; allowing for 20-25% attrition which has been reported in other studies on weight loss in PCOS, we aim to analyse 30 participants at end of treatment.

## Proposed Analyses

Recruitment, retention and adherence rates are presented with descriptive statistics. Mixed model ANOVAs will be used to determine within-group differences for continuous outcomes between baseline and 3 months, and ANCOVAs for between-group differences for continuous outcomes with baseline score as a co-variate. Intention-to-treat analysis will be used.

# Adverse Events

The Investigator is responsible for the detection and documentation of events meeting the criteria and definitions detailed below.

Participants should be instructed to contact their Investigator and/or treating acupuncturist at any time after consenting to join the trial if any symptoms develop. Treating acupuncturists will enquire about adverse events at every acupuncture visit. All reported Adverse Events (AEs) that occur between consent and the last visit for the study must be recorded in detail in the AE form. In the case of an AE, the Investigator should initiate the appropriate treatment according to their medical judgment. Participants with AEs present at the last visit must be followed up until resolution of the event.

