## Endpoints

### Primary Endpoint

Recruitment, retention and adherence rates; credibility; acceptability; and safety over the recruitment and intervention periods.

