## Control intervention

The control intervention is lifestyle intervention only (see 6.4.1below).

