#### Credibility, expectancy and perceived treatment allocation

Immediately following the first treatment, participants will complete the Credibility and Expectancy Questionnaire and question on perceived treatment allocation. This can be done online at the acupuncturist’s clinic or via email, or on paper and returned to the research assistant by fax or email.

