#### Other outcomes

- Physical activity levels will be quantified using accelerometers which will be worn by participants in the week before attending for the baseline visit, and in Week 11 (minutes per week of light, moderate and vigorous activity; number of steps per day; number of sedentary hours per day).
- Data on compliance with the lifestyle coaching program and change in dietary habits will be provided by Gethealthy NSW at baseline and 3 months.
- Participants will record the dates of their menstrual cycle using a menses calendar.
- Participants and treating acupuncturists will be provided with Adverse Events forms on which to record adverse events.

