## Detecting AEs and SAEs

All AEs and SAEs must be recorded from the time a participant consents to join the study until the last study visit.

The Investigator, treating acupuncturist and research assistant will monitor each subject for Adverse Events during the study. All Adverse Events reported between consent and final follow-up will be recorded in the AE form. The Investigator or designee will ask the subject non-leading questions in an effort to detect Adverse Events e.g.:

“How are you feeling?”

or

“Since you were last asked, have you felt unwell or different from usual?”

In addition, subjects should be encouraged to spontaneously report any unusual feelings or sensations.

Participants should also be asked if they have been admitted to hospital, had any accidents, used any new medicines or changed concomitant medication regimens. If there is any doubt as to whether a clinical observation is an AE, the event should be recorded.

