# Appendix 1 - Schedule of Observations and Procedures

| **Visit/Timepoint** | **Screening (self screening or telephone)** | **Week -1**  **(Run-in)** | **Visit 1**  **Baseline (Allocation)** | **1^st^ acupuncture treatment** | **Visit 2**  **Post intervention** |
| --- | --- | --- | --- | --- | --- |
| Week(s): | **-4 to -2** | **-1** | **0** | **1** | **12** |
| **ENROLMENT** |  |  |  |  |  |
| Eligibility screen | **X** |  |  |  |  |
| Informed Consent |  |  | **X** |  |  |
| 2hr OGTT and Insulin, free and total testosterone, SHBG, Free androgen index |  | **x** |  |  | **x** |
| Physical activity levels |  | **x** |  |  | **X (Week 11)** |
| Allocation |  |  | **X** |  |  |
| **INTERVENTIONS** |  |  |  |  |  |
| Body acupuncture + lifestyle |  |  |  |  |  |
| Auricular electro acupuncture + lifestyle |  |  |  |  |  |
| Lifestyle alone |  |  |  |  |  |
| **ASSESSMENTS** |  |  |  |  |  |
| Credibility and Expectancy Questionnaire |  |  |  | **X** |  |
| Demographic and medical questionnaire |  |  | **X** |  |  |
| Anthropometric measures and blood pressure |  |  | **X** |  | **X** |
| Concomitant Medications |  |  | **X** |  | **X** |
| Surveys – QoL, psychological, weight self efficacy, locus of control |  |  | **X** |  | **X** |
| Heart rate variability by ECG monitor |  |  | **x** |  | **x** |
| Ferriman-Gallwey score |  |  | **X** |  | **X** |
| Exit survey on acceptability of the intervention |  |  |  |  | **X** |
| Adverse Events |  |  | **X** | **X** | **X** |

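### Scheduled adverse-event enquiry and the credibility questionnaire are tied to acupuncture visits, so the lifestyle arm has no scheduled interim enquiry and no credibility score

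*Protocol*

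**What the plan says.** Section 2.2.1 of the Protocol defines the primary endpoint as "Recruitment, retention and adherence rates; credibility; acceptability; and safety over the recruitment and intervention periods", and the Study Synopsis agrees. Neither limits safety or credibility to the needled arms.

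On adverse events:
- Section 10 gives the one enquiry with a stated frequency: "Treating acupuncturists will enquire about adverse events at every acupuncture visit".
- Section 10.2 adds general surveillance: "The Investigator, treating acupuncturist and research assistant will monitor each subject for Adverse Events during the study". It continues: "The Investigator or designee will ask the subject non-leading questions in an effort to detect Adverse Events". No interval and no mode of contact are given.
- Section 7.1.1, under other outcomes, provides for self-report: "Participants and treating acupuncturists will be provided with Adverse Events forms on which to record adverse events". Section 10 also tells participants to make contact whenever symptoms develop.
- In Appendix 1 the row reads "Adverse Events | | | X | X | X". The three marks fall at baseline, the first acupuncture treatment and the post-intervention visit.

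On credibility, Sections 7.1.1 and 8.5 say: "Immediately following the first treatment, participants will complete the Credibility and Expectancy Questionnaire and question on perceived treatment allocation". The list that opens Section 7.1.1 specifies the first acupuncture treatment, and Appendix 1 gives the questionnaire a single mark in that column.

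On the comparator, Section 6.3 says: "The control intervention is lifestyle intervention only". The only trial visits common to all arms are baseline and post-intervention (Section 7.1.1).

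**The concern.** Two components of the primary endpoint are collected through a contact that one arm of three does not have.

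For safety, the chance that an event is recorded depends partly on how often and how recently a woman was asked. Section 10.1 counts any untoward event as an adverse event, whether or not it is thought to be related to the intervention, so events in the lifestyle arm matter. If two arms are questioned repeatedly and the third is not, their descriptive rates differ in ascertainment as well as in treatment.

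For credibility, participants know their allocation (Section 5.5.1) and the design is open-label (Section 3). A secondary objective is an effect size against lifestyle alone (Section 2.1.2). Differences in expectancy are then a leading rival explanation for any difference in outcome, and the schedule leaves expectancy unmeasured in the comparator. An analysis plan cannot recover data that were never collected.

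**Working it through.** **Inputs**
- Arm sizes: 13, 13 and 13 (Section 4.1); 3 × 13 = 39, as stated.
- Body acupuncture: twice weekly for two weeks, weekly for four, then three fortnightly sessions (Section 6.1.3). 2×2 + 4 + 3 = 11, which reproduces the stated total. The Synopsis gives 12 treatments on a different schedule (2×4 + 4 = 12).
- Auricular electro-acupuncture (AEA): stated total 6 (Section 6.2.3). The schedule in the same sentence gives 2×2 + 4 = 8, so the stated total is not reproduced. Section 8 repeats 11 and 6 in its adherence definition. These passages must be reconciled; both AEA counts are carried below.
- Lifestyle alone: no acupuncture visits. Up to 13 coaching calls are planned in every arm (Section 6.4.1), but no adverse-event question is attached to them.

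**Scheduled contacts after baseline, following the plan as written**

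| | Body acupuncture | AEA | Lifestyle |
|---|---|---|---|
| Interim adverse-event enquiries per woman | 11 | 6 (or 8) | 0 |
| Including week 12 | 12 | 7 (or 9) | 1 |
| Interim enquiries per arm of 13 | 13×11 = 143 | 13×6 = 78 (or 13×8 = 104) | 0 |
| Credibility questionnaires per woman | 1 | 1 | 0 |

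Enquiry is unequal between the two needled arms as well as against lifestyle.

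**Recall window.** The sample question in Section 10.2 asks about the time since the previous enquiry. At week 12 that can span up to 12 weeks for a lifestyle woman who has not been asked in between, but about two weeks for needled women, whose last sessions are fortnightly.

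**Credibility.** Women who can be scored: 13 + 13 = 26 of 39, or 67%. In the lifestyle arm the count is 0 of 13. This needs no assumption beyond following the schedule.

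**What unequal ascertainment could do (assumed values, not from the documents).** Let the true risk p of at least one event per woman be equal in all arms. Let capture be c₁ = 0.90 under repeated enquiry, and c₀ under self-report plus one week-12 enquiry. Expected women with a recorded event = 13 × p × c; apparent risk ratio = c₁/c₀, whatever p is.

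| c₀ | Apparent ratio | Needled arm, p = 0.20 | Lifestyle arm, p = 0.20 |
|---|---|---|---|
| 0.90 | 1.0 | 2.34 of 13 | 2.34 of 13 |
| 0.70 | 1.29 | 2.34 | 1.82 |
| 0.50 | 1.8 | 2.34 | 1.30 |
| 0.30 | 3.0 | 2.34 | 0.78 |

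At c₀ = 0.30 the counts are 1.17 against 0.39 for p = 0.10, and 3.51 against 1.17 for p = 0.30.

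**The case against.** A reader might infer that nobody asks lifestyle women about adverse events before week 12. The documents do not support that. Section 10.2 has the investigator and research assistant monitor and question every participant, all women receive adverse-event forms, and all may report at any time. What is missing is a scheduled interim enquiry for that arm. Nor can the Appendix 1 row prove the point: it marks only the first acupuncture treatment, whereas Section 10 requires enquiry at every one, so the row is not exhaustive.

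A reader might also infer that a planned comparison is distorted by a known amount. That goes too far as well. The primary endpoint is analysed descriptively (Synopsis; Section 9.2), group differences are named only for secondary endpoints (Section 2.2.2), and no between-arm test of safety or credibility is stated. If self-report captures events as well as repeated enquiry does, there is no bias. Counting each prompt as an equal, independent chance of a report would exaggerate the effect, because a single later question can cover the whole interval.

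The risks that Sections 10.3 and 10.4 describe are those of needles and device, so asking at treatment visits suits part of the feasibility question. Coaching is given in every arm, so rating only the added treatments is a defensible choice; but Section 2.2.1 states no such restriction, and Sections 7.1.1 and 8.5 refer to participants in general.

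What remains is that the general monitoring has no interval, and that self-report is open to all arms and so does not offset the extra prompting in two of them. Describing rates without testing them does not make them comparable. The perceived-allocation question tells little when women know their arm, but it is not a named endpoint and this point does not rest on it.

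**Conclusion.** The point holds in a limited form and is worth correcting.

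- **Safety:** scheduled interim enquiry is 11, 6 (or 8) and 0 per woman, so by-arm adverse-event rates are not like for like. The likely direction is relative over-recording in the acupuncture arms. The size cannot be fixed from the documents; under the assumptions above the apparent ratio runs from 1.0 to 3.0, with no true difference between arms.
- **Credibility:** no score is scheduled for 13 of 39 women, so credibility and expectancy cannot be compared with lifestyle alone. This follows directly from the schedule.

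No sample size is affected.

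**What to change.** 1. Put the same short adverse-event questionnaire to all three arms at the same fixed weeks, online through the REDCap system already in use, and add those weeks to Section 10.2 and Appendix 1.
2. Base by-arm safety summaries on that questionnaire. Keep practitioner enquiry, and report the events it elicits separately for the two acupuncture arms.
3. Give the credibility and expectancy questionnaire to all arms at a matched point: the first body acupuncture or AEA treatment, or the first coaching call for lifestyle. All 39 women could then be scored.
4. Reconcile the treatment counts in Section 6.2.3, and those in the Synopsis with Section 6.1.3, since they set the number of practitioner enquiries.

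The cost is amendment wording, a few extra brief online forms and a small added burden on participants. Treatment and sample size do not change.
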